#### Sensitivity Analysis

Sensitivity analysis will be conducted to assess the impact of missing data on our results. We will estimate whole-scale missing data due to loss to follow-up using multiple imputation by chained equation. This will allow us to conduct a strict ITT for all respondents who took part at baseline. Following recent guidelines, we will also conduct a sensitivity analysis that will take into account the partially nested design of the study and, therefore, assess the potential impact of the “therapist effect” on our results [46]. Further analysis will be conducted to adjust for potential confounders, including sex and age.

A per-protocol analysis will serve as a further sensitivity analysis to investigate the robustness of the conclusions of the primary analysis, following departures from the randomized intervention policies. This will exclude those participants in the control arm who used a GET self-help approach. Subgroup analyses including only those meeting the Oxford or CDC criteria for CFS will also be undertaken. We will analyze moderators of improvement, such as these criteria, but also depression and severity of physical function and fatigue. These subgroup analyses are exploratory and will be interpreted with due caution [47].

#### Analysis for Hypotheses 2 and 3

Chi square will be used to describe any difference in satisfaction (ie, satisfied vs nonsatisfied) across treatment arms and any differences in SAEs, SARs, or serious deterioration (1+ vs none) across treatment arms.

The above plan is what we intend to do; however, the final analyses reported may differ from those planned, allowing for *post hoc* analysis where it is indicated [48]. We will report alternative methods if statistical models do not converge, and omit planned analyses that are superseded, redundant, or no longer of interest. We will report any changes in consequent papers.

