#### 12-Months Post-randomization

The primary purpose of the 12-month follow-up will be to obtain the health-economic assessment (see section below); however, we will also collect data on the primary outcome measures and the CGI so that we can assess longer-term physical functioning, fatigue, and change in overall health and CFS. The following information will be collected via questionnaires sent in the mail with a stamped addressed envelope for return: CFQ, SF-36 PF, CGI, EQ-5D, and CSRI.

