#### Safety Measures and Reporting

For safety outcomes, we will include serious adverse events (SAEs), serious adverse reactions to trial treatments (SARs), and serious deteriorations (SDs). SAEs will be defined according to usual clinical trial definitions (ie, an event that is fatal, life-threatening, or results in or prolongs hospitalization; an increase in severe and persistent disability or incapacity; self-harm; or any other important condition that may require medical or surgical intervention to prevent the above [10] and will be reported to the appropriate authorities in the standard manner. SARs are SAEs that are considered to be a reaction to any trial therapy or drug prescribed. SDs will be defined as any of the following outcomes: CGI scores of 6 and 7, active withdrawal from the intervention due to worsening, or a reduction on the SF-36 PF scale by 10 or more points. Participants will record any nonserious adverse events (NSAEs) in their follow-up questionnaire. An adverse event is defined as any clinical change, disease, or disorder recorded by the participant, whether or not it is considered to be related to the trial or its treatments. Participants will be asked to record whether they believe the adverse event was “related to following the GET guide.” In the event of an adverse event (AE), the center leader will judge the seriousness of the event, and, if judged to be serious, the relationship to a trial supplementary therapy or SMC prescribed treatment, and the expectedness of the event. The trial manager will report all SAEs to the principal investigator (PI) within 24 hours, regardless of the relationship to trial treatment. Reporting of SAEs and SARs will be carried out according to normal regulatory research governance requirements.

After an SAE or SAR, the center leader will make a decision as to whether the participant should be withdrawn from either randomized treatment or from the trial, or if an alteration in their SMC is needed; arrangements will be made for further assessment and management as required. The trial manager will provide the center leader with monthly follow-up reports until resolution. These reports will be communicated to the Data Monitoring and Ethics Committee (DMEC), and other appropriate authorities via the trial manager.

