#### Sample Size

Our original sample size was based upon the SF-36 PF as our primary outcome; however, the significance level was reduced to 2.5% to accommodate 2 primary outcomes [31]. A large previous trial of CFS/ME using the SF-36 PF (the PACE trial) indicated a baseline mean score of 37 (SD 15) and an outcome score of 48 (SD 21) following 12 weeks of practitioner-led GET, an 11-point increase [11]. Based on these previous findings, and our estimate that GES will be less effective than GET, the sample size calculations are based on the assumption that a mean difference of 8 (SD 18) points between intervention arms at the 12-week follow-up will be a clinically useful difference on the SF-36 PF scale after 12 weeks [11]. Thus, assuming a significance level (alpha) of 2.5% and power of 80%, we require a minimum of 98 participants in each group. This sample size will be upwardly adjusted to allow for loss to follow-up and other compliance issues. Based upon previous trials, we expect about 10% loss to trial follow-up [17]; therefore, we will recruit 109 patients in each group (a total of 218).

Based on a previous trial of GET, in which the difference between baseline and 12 weeks was 5.4 points on the CFQ [11], we assume that a mean difference of 3 (SD 6) points will represent a clinically useful difference at the 12-week follow-up. Hence, assuming a significance level (alpha) of 2.5% and power of 80%, we require a total of 174 patients, which is less than the 218 to be recruited, so adequate power will be achieved.

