#### Missing Data

Item-level missing data on the primary and secondary outcome variables at baseline and follow-up will be imputed using mean replacement (prorating). Prorating will be implemented only when less than 20% of item responses per scale are missing. The reasons for missing baseline and follow-up whole-scale data will be summarized using the CONSORT diagram. We will identify baseline characteristics associated with missing data to allow us to impute data to do sensitivity analyses.

#### Analysis for Hypothesis 1

Our primary intention-to-treat analysis will compare the SF-36 PF and CFQ at 12 weeks between groups adjusted using multivariable linear regression analyses [45]. Intention-to-treat (ITT) analyses will be conducted on data from all randomized participants with information at follow-up (ie, modified ITT) regardless of any departure from the allocated treatment arm. We will adjust for our stratification factors (depression, center, and severity of disability) as well as baseline values of outcomes and treatment arm.

A secondary analysis will explore the association between treatment arm and having achieved a clinically useful improvement on the SF-36 PF (ie, an 8-point increase) and the CFQ (ie, a 3-point decrease) using chi-squared analysis.

Analysis of the secondary outcome, the CGI, will compare the proportions scoring “much” or “very much” better (1 and 2), the proportions scoring “a little better,” “no change,” or “a little worse” (3 to 5), and the proportions scoring “much” or “very much” worse (6 and 7) across treatment arms, using an ordinal logistic regression adjusting for our stratification variables.

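### The only planned check on missing 12-week outcomes assumes missing at random, much as the primary analysis does, so agreement between them says little about outcome-related loss

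*Protocol article*

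**What the plan says.** Under Analysis for Hypothesis 1, the protocol article bases the primary regression on "data from all randomized participants with information at follow-up (ie, modified ITT) regardless of any departure from the allocated treatment arm". The model adjusts for the stratification factors, the baseline value of the outcome and treatment arm.

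Two statements cover whole-scale missing outcomes:

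- Missing Data: "We will identify baseline characteristics associated with missing data to allow us to impute data to do sensitivity analyses".
- Sensitivity Analysis: "We will estimate whole-scale missing data due to loss to follow-up using multiple imputation by chained equation". The section gives the aim as gauging how missing data affect the results, and says that the imputation permits a strict intention-to-treat analysis.

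The other analyses listed there concern the therapist effect, adjustment for sex, age and other potential confounders, a per-protocol set and subgroups. None of them deals with missing outcomes. The missing-data assumption is not named, and no analysis departing from missing at random is stated.

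On the expected amount, Sample Size says "we expect about 10% loss to trial follow-up", without a split by arm. Non-Responders describes telephone, then email or text, contact to obtain at least the two primary outcomes and the CGI. It also provides for usual data collection from people who stop treatment but stay in the trial.

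**The concern.** A sensitivity analysis is informative when it changes the assumption in doubt. Here the doubtful assumption is that, given baseline data and arm, participants without 12-week scores would have scored like those who returned them. The complete-case regression makes that assumption. Standard chained-equation imputation, with only the 12-week outcome missing and baseline variables as predictors, makes nearly the same one: a lost GES participant is imputed with the GES benefit seen in those who stayed.

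Outcome-related loss is plausible in this design. Participants know their allocation, the outcomes are self-rated, and the questionnaires arrive by mail. If GES participants who did badly were less likely to reply, both planned estimates would lean the same way, towards GES, on both primary outcomes. Their agreement could then be reported as robustness that had not been tested.

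**Working it through.** **1. The plan's own figures.** Inputs from Sample Size: SF-36 PF difference 8, SD 18; CFQ difference 3, SD 6; alpha 2.5% (sidedness not stated, taken as two-sided, z = 2.241); power 80% (z = 0.842); 10% loss.

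- SF-36 PF: n = 2 × (2.241 + 0.842)² × (18/8)² ≈ 96.2, so 97 per arm, or 98 with the t distribution. 98/0.9 = 108.9, so 109 per arm and 218 in total, as stated.
- CFQ: 2 × (2.241 + 0.842)² × (6/3)² ≈ 76.0, so 77 per arm, or 78 with the t distribution. 78/0.9 = 86.7, so 87 per arm and 174 in total, as stated.

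The sample size is not in question.

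**2. Does the imputation add information about informative loss?** This was checked by simulation: 109 per arm, true effect zero, baseline mean 37 and SD 15, 12-week SD 18, assumed baseline–outcome correlation 0.5. Loss was 16 GES participants, mainly those with the worst change, and 5 SMC participants at random (about 15% and 5%). Mean estimates over 1,500 replicates:

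| Analysis | Mean GES effect (SF-36 PF points) |
|---|---|
| Full data | 0.0 |
| Complete-case regression | +3.4 |
| Imputation from the baseline score | +3.4 |

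The last two differed by 0.12 on average in absolute value. The size and direction of the bias follow from the assumed loss mechanism. What the check shows is that the imputation removed none of it.

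**3. How large must the departure be?** Just-significant unadjusted difference = z × SD × √(2/98):

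- SF-36 PF: 2.241 × 18 × 0.1429 = 5.76.
- CFQ: 2.241 × 6 × 0.1429 = 1.92.

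If a fraction p of the GES arm is missing and truly scores D points worse than its missing-at-random prediction, the estimate falls by p × D. Significance is lost at D = (planned difference − just-significant difference)/p:

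| GES loss p | SF-36 PF shift | CFQ shift |
|---|---|---|
| 10% (planned rate, evenly spread) | 2.24/0.10 = 22.4 | 1.08/0.10 = 10.8 |
| 15% (assumed) | 14.9 | 7.2 |
| 20% (assumed; all of the planned 10% overall loss in GES) | 11.2 | 5.4 |

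At 10% loss these shifts equal 22.4/18 = 1.2 SD and 10.8/6 = 1.8 SD. The calculation holds the standard error at 98 per arm and ignores imputation variance.

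**4. Effect of baseline adjustment.** With an assumed correlation of 0.6, the residual SD is 18 × 0.8 = 14.4 and the just-significant SF-36 PF difference is 2.241 × 14.4 × 0.1429 = 4.61. The tipping shifts become 3.39/0.10 = 33.9 and 3.39/0.15 = 22.6.

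**5. A shift tied to the plan's own threshold.** Suppose lost GES participants forgo the 8 points and also fall by 10, the SF-36 PF drop that the plan counts as serious deterioration, while SMC is unchanged. The shift is then 18. At 10% GES loss the effect is 8 − 1.8 = 6.2, above 5.76. At 15% it is 8 − 2.7 = 5.3, below 5.76 but above 4.61.

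**The case against.** Several points count against a stronger claim, and most of them stand.

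- A reader might infer from the safety criterion "active withdrawal from the intervention due to worsening" that the plan itself expects worsened GES patients to go missing. It does not say so. That criterion concerns stopping treatment, and Non-Responders provides for collecting outcomes from such people. The primary analysis also keeps them whatever treatment they took.
- A reader might infer that the imputation excludes post-baseline data. The article names only baseline inputs, but it gives no full variable list and rules nothing out. At 12 months "we will also collect data on the primary outcome measures and the CGI", and the physiotherapist rates GES participants after the last session. Even so, 12-month scores may reflect service therapy started after week 12, the therapist ratings exist in one arm only, and nothing shows that people lost at 12 weeks return later.
- Exact agreement between the two analyses is not guaranteed. The simulation used a single baseline covariate. The trial collects many baseline measures outside the primary model, and conditioning on them could move the estimate. It would still not test missing-not-at-random loss.
- The plan would not be blind to the problem. Reasons for missing data go into the CONSORT diagram, and serious deterioration is compared between arms. These give hints, but they do not measure the effect on the primary estimates.
- An unseen analysis plan might add such an analysis. However, this article chooses a method and states its purpose, and the method falls short of that purpose. That is more than detail left for later.

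**Conclusion.** The point holds in a limited form. The one stated analysis of missing outcomes stays within missing at random and largely repeats the assumption of the primary regression, so it cannot show bias from outcome-related loss. This inference rests on how standard chained-equation imputation works, since the article does not name its assumption.

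It would be wrong to conclude that the primary result is likely to be overturned. With 10% loss spread evenly, an observed 8-point SF-36 PF difference tips only at a shift of about 22 points, and a 3-point CFQ difference at about 11. Baseline adjustment raises these. The risk becomes material mainly if loss exceeds the plan or falls mostly in GES; at an assumed 15% GES loss the unadjusted figures are about 15 and 7 points. The loss split, the correlations and the loss mechanism are assumptions. The direction of any bias is plausible but not established by the document.

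**What to change.** Keep the modified intention-to-treat regression as primary, and keep the chained-equation imputation, labelled as a missing-at-random analysis. Add to Sensitivity Analysis a prespecified missing-not-at-random analysis for both primary outcomes:

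1. Start from the missing-at-random imputations and shift the imputed values separately by arm, SF-36 PF downward and CFQ upward. The range should be wide enough to reach the tipping point; at an even 10% loss a range ending at 18 SF-36 PF points would stop short of it.
2. Report the shift at which each 2.5% conclusion is lost, next to the observed loss in each arm.
3. Optionally, impute missing GES participants as SMC as one separate scenario. It should not be the base for the shifts if their range already includes the 8-point lost benefit, which would then be counted twice.
4. Optionally, add the physiotherapist ratings and 12-month scores as auxiliary variables, noting that 12-month scores may reflect later service therapy.
5. Do not describe agreement with the missing-at-random imputation as evidence of robustness to informative loss.

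The cost is wording and a little more programming, with no new data or visits. The downside is a wider and less favourable sensitivity range.

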### Hypotheses

First, we will test the null hypothesis that GES plus specialist medical care (SMC) will be no more effective at improving either physical disability or fatigue than usual SMC alone, as shown by no statistically significant difference between the two arms of the trial 12 weeks after randomization. Second, we will test the hypothesis that GES will be acceptable to patients diagnosed as having CFS/ME in specialist secondary care clinics, as demonstrated by less than 25% of eligible patients declining participation in the trial, and more than 75% of those participating being satisfied with the approach. Third, we will assess the difference in the number of participants suffering serious adverse effects, serious adverse reactions, or a serious deterioration across the study arms.

We will also assess whether there is a statistically significant difference in cost-effectiveness between the two interventions, although this is not a hypothesis.

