#### 12-Weeks Post-randomization

The main outcome end-point will be 12 weeks after randomization, before patients begin their service therapy. We chose 12 weeks as this was about the length of the waiting list for therapy at the St Bartholomew’s CFS service at the time of application for funding. At the end-point, the following information will be collected via questionnaires sent by mail with a stamped addressed envelope: SF-36 PF, CFQ, self-rated Clinical Global Impression of Change (CGI) [39] (this will be done once for overall health and then a second time specifically for CFS), HADS, EQ-5D, WSAS, IPAQ, CSRI, and PHQ-15. Participants will be asked to describe the following: whether they have used any of 4 listed self-help resources since randomization, including the unpublished GES guide [40-42]; how satisfied they are with the help they received; how closely they followed the GES guide; their current employment status and whether they have had to reduce/stop work due to their CFS/ME; any new health problems not already reported; and whether they are taking antidepressant medication for any reason.

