#### Descriptive Statistics for Primary and Secondary Outcomes

Box plots will be used to assess the data distribution of continuous measures. Descriptive statistics will be broken down by intervention group at baseline and follow-up. Normality of the scales and regression residuals will be explored using diagnostic plots, and if the assumption of normality is violated, the data will be transformed. We will present means and standard deviations for all normally distributed measures, and medians and quartiles for nonnormal measures. Discrete outcomes will be described using both number and percentage.

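### The satisfaction analysis listed for hypothesis 2 compares the arms, whereas the hypothesis sets a fixed 75% criterion for GES, and no named analysis ties the GES percentage to it

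*Protocol article*

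**What the plan says.** The Hypotheses section of the Protocol article states the second hypothesis as a claim about GES itself: "we will test the hypothesis that GES will be acceptable to patients diagnosed as having CFS/ME in specialist secondary care clinics". It attaches two fixed benchmarks. One concerns uptake, "as demonstrated by less than 25% of eligible patients declining participation in the trial". The other, which is the subject here, concerns satisfaction: "more than 75% of those participating being satisfied with the approach".

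The analysis is given under Analysis for Hypotheses 2 and 3. For satisfaction it reads: "Chi square will be used to describe any difference in satisfaction (ie, satisfied vs nonsatisfied) across treatment arms". The same sentence applies the same test to serious adverse events, serious adverse reactions and serious deterioration, which belong to hypothesis 3.

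Two other places bear on the point. The 12-week questionnaire asks participants "how satisfied they are with the help they received". The section on descriptive statistics for primary and secondary outcomes plans summaries by intervention group and adds: "Discrete outcomes will be described using both number and percentage".

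**The concern.** A between-arm chi-square tests whether two proportions are equal. Hypothesis 2 asks whether one proportion, that in the GES arm, is above 75%. The result of the first does not answer the second. Hypothesis 3 is framed as a difference between arms, so the test suits it. Hypothesis 2 is not framed that way, yet it shares the sentence.

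This is not a detail left to an unseen analysis plan. The article names a method for hypothesis 2, and that method addresses another question.

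The denominator is also loosely worded. Taken literally, those participating includes the SMC arm, which has no access to the booklet during the trial. The item asks about help received, so an SMC answer describes SMC and not GES.

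What is at stake is the acceptability claim. The abstract's conclusions and the Discussion both make acceptability one of the conditions for putting the booklet on the Internet. A reader of the results would want to see the GES percentage, its precision and the 75% benchmark together.

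**Working it through.** **Number per arm.** The Sample Size section says: "assuming a significance level (alpha) of 2.5% and power of 80%, we require a minimum of 98 participants in each group", for "a mean difference of 8 (SD 18) points between intervention arms at the 12-week follow-up".
- Normal approximation, two-sided: n = 2 × (2.2414 + 0.8416)² × 18² / 8² = 96.2, rounded up to 97.
- Based on the t distribution: 97.5, rounded up to 98, as stated.
- With 10% loss: 98 / 0.9 = 108.9, rounded up to 109 per arm, 218 in total, as stated.

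These figures reproduce. No sample size is stated for hypothesis 2, so I use 98 evaluable per arm.

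**Assumed rates.** The documents give no satisfaction rate for this trial. The counts below are illustrations and not predictions.

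**Formulas.** Pearson chi-square without continuity correction: χ² = (p1 − p2)² / [p(1 − p) × 2/n], where p is the pooled proportion. The interval for the GES proportion is the exact (Clopper-Pearson) 95% CI.

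**Case A: GES 59/98, SMC 39/98.**
- p1 − p2 = 20/98 = 0.2041; pooled p = 98/196 = 0.5.
- χ² = 0.2041² / (0.25 × 2/98) = 8.16, p = 0.004.
- GES proportion 60.2%, exact 95% CI 49.8% to 70.0%.
- The arms differ clearly, and the whole GES interval lies below 75%.

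**Case B: GES 83/98, SMC 78/98.**
- p1 − p2 = 5/98 = 0.0510; pooled p = 161/196 = 0.8214.
- χ² = 0.0510² / (0.8214 × 0.1786 × 2/98) = 0.87, p = 0.35.
- GES proportion 84.7%, exact 95% CI 76.0% to 91.2%.
- No difference is shown between the arms, and the whole GES interval lies above 75%.

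Continuity correction gives p = 0.007 in case A and p = 0.46 in case B. With 109 per arm the uncorrected values are p = 0.004 (65 against 44) and p = 0.28 (93 against 87). The pattern does not change.

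**Precision of a percentage near the benchmark.** The smallest count above 75% of 98 is 74 (75.5%). Its exact 95% CI is about 66% to 84%. A percentage just over the line is therefore compatible with true satisfaction well below it, which is why an interval should be shown.

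**What a lower-limit rule would demand.** The smallest count whose exact lower limit exceeds 75% is 83/98 (82/98 gives 74.8%, 83/98 gives 76.0%). At a true rate of 82%, the GET satisfaction quoted in the Background, the two possible rules behave as follows:
- at least 83/98 (lower limit above 75%): met 29% of the time;
- at least 74/98 (observed percentage above 75%): met 96% of the time.

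At a true rate of exactly 75%, the observed-percentage rule is met 51% of the time and the lower-limit rule 1.5% of the time.

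**The case against.** The strongest defence is that the decision rule already exists. The Hypotheses section sets the benchmark and the descriptive section plans percentages by group, so the GES figure can be set against 75% without any test. The chi-square is offered only to describe a difference, and nothing says that its p-value decides acceptability. All of this stands, and it keeps the point small. It does not remove the mismatch: the hypothesis is said to be tested, and the only satisfaction analysis listed under its own heading does not address it.

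A reader might infer three stronger things that the documents do not support.
- *That the chi-square could overturn the criterion or point the opposite way.* In case A the 75% benchmark is still missed, and in case B it is still met, whatever the p-value. The test and the criterion answer different questions; they do not conflict.
- *That SMC answers would be pooled in to decide whether GES is acceptable.* No section proposes pooling. The sentence is about GES, and the one analysis named keeps the arms apart. The wording is ambiguous and no more than that.
- *That the lower confidence limit must exceed 75% before acceptability can be called demonstrated.* The Hypotheses section sets a benchmark and does not say this. Such a rule raises the observed bar to 85% and, as shown above, would often fail at a true rate of 82%. It is a trade-off for the sponsor.

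**Conclusion.** The point holds as a mismatch between a stated hypothesis and the analysis named for it. The between-arm chi-square cannot show whether more than 75% of GES participants are satisfied. The percentage will be available from the descriptives by group, but no named analysis links it to the criterion or reports its precision.

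The mismatch itself rests on the text alone. The illustrations rest on assumed satisfaction rates and 98 evaluable participants per arm. Severity is minor: satisfaction is one of the two parts of hypothesis 2, no estimate is biased, no data are lost, and the analyses of physical function and fatigue are unaffected.

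**What to change.** - Under Analysis for Hypotheses 2 and 3, state that the satisfaction part of hypothesis 2 is assessed in participants allocated to GES, as the proportion satisfied with an exact 95% CI, set against 75%.
- Keep the between-arm chi-square for satisfaction as descriptive context only.
- In Hypotheses, make the denominator those allocated to GES.
- Let the sponsor state whether the benchmark is judged on the observed percentage or on the lower confidence limit, knowing the trade-off shown above.

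The cost is about two sentences of wording. It needs no new data, because the 12-week satisfaction item already supplies what is required.

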**Conclusions:**

This study will indicate whether adding GES to SMC will benefit patients who often spend many months waiting for rehabilitative therapy with little or no improvement being made during that time. The study will indicate whether this type of guided self-management is cost-effective and safe. If this trial shows GES to be acceptable, safe, and comparatively effective, the GES booklet could be made available on the Internet as a practitioner and therapist resource for clinics to recommend, with the caveat that patients also be supported with guidance from a trained physiotherapist. The pragmatic approach in this trial means that GES findings will be generalizable to usual National Health Service (NHS) practice.

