## Discussion

CFS/ME is a relatively common and frequently disabling condition with limited treatment options of proved efficacy available within the NHS. GET is recommended, but access to it is limited, with patients often spending many months waiting for rehabilitative therapy with no help given during that time. The longer someone has CFS/ME, the worse the prognosis [6].

Guided exercise self-help (GES) has never been tested in a randomized controlled trial for CFS/ME. It is important for people with CFS and the NHS to know whether GES is more effective, and cost-effective, when used with SMC, than when SMC is used alone.

If this trial shows GES to be acceptable and safe, and shows a clinically useful difference between arms, then the GES booklet will be made available on the Internet and through other media as a practitioner resource, with the knowledge that it is an acceptable, safe, and effective treatment when supported by advice from a trained therapist. If found to be cost-effective, then it could be recommended for commissioners of services. It could be used as a first line of treatment while patients are waiting for face-to-face specialist practitioner-delivered therapies, such as GET and CBT. Guided self-help exercise could become the first step in a stepped-care approach for CFS/ME in the NHS, by training current physiotherapists to deliver it.

The next trial would be to test this intervention in primary care, which could immediately follow this trial. The secondary care trial is necessary first, to ensure this intervention is effective in those with properly diagnosed CFS/ME, before testing it in those at the primary care level, where the diagnosis is not so well-established [57].

If shown to be an effective treatment, this policy of providing a guided self-help approach to initially stabilize and then increase PA in patients with CFS/ME could also be tested for patients with many other chronic disabling conditions known to respond to practitioner-delivered graded exercise approaches, including arthritis, chronic obstructive airways disease, and diabetes mellitus [58].

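### The protocol promises a verdict that GES is safe but sets no criterion for it, and the difference test it names for serious harms could not support that verdict at 98 to 109 per arm

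*Protocol article*

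**What the plan says.** Safety is a promised conclusion. The Abstract (Conclusions) states: "The study will indicate whether this type of guided self-management is cost-effective and safe". The Discussion attaches an action to it, in a sentence that opens: "If this trial shows GES to be acceptable and safe, and shows a clinically useful difference between arms, then the GES booklet will be made". The same sentence goes on to online release of the booklet, "with the knowledge that it is an acceptable, safe, and effective treatment when supported by advice from a trained therapist".

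The Hypotheses section treats acceptability and safety differently. Acceptability has thresholds: "less than 25% of eligible patients declining participation in the trial, and more than 75% of those participating being satisfied with the approach". For safety it says only that "we will assess the difference in the number of participants suffering serious adverse effects, serious adverse reactions, or a serious deterioration across the study arms".

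Under Analysis for Hypotheses 2 and 3, a chi-square is to describe "any differences in SAEs, SARs, or serious deterioration (1+ vs none) across treatment arms". Safety Measures and Reporting counts any one of three events as serious deterioration, the last being an SF-36 PF fall of at least 10 points: "CGI scores of 6 and 7, active withdrawal from the intervention due to worsening, or a reduction on the SF-36 PF scale by 10 or" (the quote stops just short of the end of that threshold).

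The Sample Size section covers SF-36 PF and CFQ only. The article gives no expected rate, tolerable excess or upper bound for any safety outcome.

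**The concern.** To conclude that a treatment is safe is to conclude that any excess of harm is smaller than some stated amount. A test of difference does not do this: a non-significant result fits both no excess and a large excess that the trial was too small to show. The article fixes the conclusion and its consequence but not the amount, so nothing tells a reader which result would count as safe and which would not.

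The question is contested in this population. The Background cites a survey in which 56% of those who had received GET reported feeling worse. Without a criterion, the booklet could be released as safe while the trial's data remain compatible with a sizeable excess of serious deterioration or serious adverse events in the GES arm.

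**Working it through.** **1. The plan's own sample size.** Inputs from Sample Size: difference 8, SD 18, alpha 2.5% (taken as two-sided), power 80%. Normal formula: n = 2 × 18² × (2.241 + 0.842)² / 8² = 96.2, so 97 per arm. The t-based version gives 97.5, so 98, as stated. With 10% loss, 98 / 0.9 = 108.9, so 109 per arm and 218 in total. The plan's figure reproduces. The safety comparison therefore rests on 98 to 109 per arm.

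**2. Power of the chi-square to show a doubling.** The protocol gives no control rate and no significance level for safety. I assume a two-sided 5% level and a range of control rates. Method: enumerate all pairs of counts from two independent binomials, apply the uncorrected Pearson chi-square, and add the probability of the significant results in the direction of harm.

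| Control → GES | 98 per arm | 109 per arm |
|---|---|---|
| 1% → 2% | 5% | 6% |
| 2% → 4% | 11% | 12% |
| 5% → 10% | 26% | 30% |
| 10% → 20% | 51% | 56% |
| 15% → 30% | 72% | 77% |
| 20% → 40% | 87% | 91% |
| 25% → 50% | 96% | 97% |

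**3. Where serious deterioration may lie.** The SF-36 PF component can be gauged from the SDs in Sample Size (15 at baseline, 21 at 12 weeks). These come from a GET trial, so applying them to controls is an assumption. SD of change = √(15² + 21² − 2ρ × 15 × 21).
- ρ = 0.5, mean change 0: SD = √351 = 18.7; P(fall ≥ 10) = Φ(−10/18.7) = 30%.
- ρ = 0.8, mean change +5: SD = √162 = 12.7; P = Φ(−15/12.7) = 12%.

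At ρ = 0.9 the range is 7-16%. So 12-30% is plausible for this component alone, though not certain.

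**4. A 10-point excess at such rates.** Doubling 15-25% is a very large harm, so I also took a fixed excess of 10 points, by the same enumeration.

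| Control → GES | 98 per arm | 109 per arm |
|---|---|---|
| 15% → 25% | 42% | 46% |
| 20% → 30% | 37% | 41% |
| 25% → 35% | 34% | 37% |

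**5. What an equal split would exclude.** Suppose 20/98 (20.4%) in each arm. The Wilson 95% limits are 13.6% and 29.4%. Newcombe upper limit for the difference = √[(29.4 − 20.4)² + (20.4 − 13.6)²] = √(9.0² + 6.8²) = 11.3 points. The same method with 10/98 in each arm gives 8.8 points.

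**6. A non-significant split.** With 10/98 on SMC and 19/98 on GES, the pooled rate is 29/196 = 14.8%, chi-square = 3.28 and p = 0.07. The observed excess is 9.2 points, with a Newcombe 95% interval of −0.9 to +19.2.

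**The case against.** The strongest reply is that the article never says a non-significant chi-square will be read as safe. A reader might infer that it will, but the text does not support this: the chi-square is there to describe differences, hypothesis 3 is not framed as a null hypothesis with a significance rule, and the Discussion sentence is conditional.

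Nor is the chi-square the only safety strand. The CGI is said to capture safety as well as efficacy and goes into an adjusted ordinal regression; the DMEC can look at SAEs by arm; two independent scrutineers review event classification. This stands. However, the regression is another analysis of difference, and monitoring and classification set no limit on excess harm, so none of them supplies the missing criterion.

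A reader might also infer that the test misses a doubling of serious harm half to nine times in ten whatever the outcome. That holds only for assumed control rates of about 2-10%, which may suit SAEs and SARs. Serious deterioration is an any-of composite and may well be commoner; at 15-25% a doubling would be found 72-97% of the time. What remains there is the weak power for a 10-point excess and the width of the interval.

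Finally, trials are not normally powered on safety, so the sample size is no error. Whether an interval accompanies the chi-square is commonly left to the statistical analysis plan, which is not shown. Both points are fair. But an interval elsewhere would not say what upper limit counts as safe, and the article itself states the claim, its consequence and a criterion for the parallel claim of acceptability.

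**Conclusion.** The point holds in this form: the protocol commits to a conclusion on safety and ties booklet release to it, sets no criterion for that conclusion, and names for the serious harms a between-arm test that cannot show absence of harm.

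The size depends on control rates that the protocol does not give. Power for a doubling runs from 11-12% at a 2% control rate to 87-91% at 20%. For a 10-point excess from 15-25% it is 34-46%. Even an exactly equal split of 20/98 leaves an excess of up to 11.3 points open. These figures assume 98 to 109 per arm, a two-sided 5% level and no continuity correction; a correction would lower power (to 42% for 10% against 20% at 98 per arm).

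The documents do not show that the trial will equate non-significance with safety. They show that they state no rule against doing so and no other criterion. It should be corrected, but it does not touch the primary efficacy analysis.

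**What to change.** In Analysis for Hypotheses 2 and 3, base hypothesis 3 on the GES-minus-SMC risk difference with a two-sided 95% confidence interval (Newcombe or Miettinen-Nurminen), separately for SAEs, SARs and serious deterioration. Keep the chi-square as description.

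Have the TSC/DMEC fix a tolerable excess before unblinding. In the Abstract conclusions and the Discussion, allow the word *safe* only if the upper confidence limit lies below that figure. Otherwise report that no excess of harm was shown and that an excess of up to X percentage points is not excluded, with X the observed upper limit.

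The margin needs one definition of serious deterioration. Safety Measures and Reporting counts active withdrawal due to worsening, while the 12-Week Follow-Up paragraph of the economic section counts active withdrawal without that condition; the two must be reconciled first.

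The cost is some wording and one agreed figure, with no extra patients or data. The downside is that the trial may be unable to use *safe* without qualification.
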